### 8.7 Blinding

All follow-up research data will be routinely collected by the UNIEXE Qualtrics system, with the system sending reminders by email and text message. The Lead Researcher will undertake the initial analysis which will be discussed with the wider research team and agreed with the written analysis section by the Trial Steering Committee. Participants and data analysts will be blinded.

[name] (Iona Mind) will provide a set of download codes for group A and group B. The researchers will not know which group of codes contains the access to the intervention or control arm. The researchers will randomly allocate these codes to eligible participants in blocks of 3.

Accidental unblinding may occur if one of the research team receives an email from a participant with questions or comments containing identifiable information about the treatment arm they are in. If this happens, the researcher will notify the research team and will not conduct any analysis to allow the blinded researchers to conduct the analysis.

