### 8.3 Consent

Potential participants will be initially routed to, or seek out, the UNIEXE Qualtrics page and will be provided with the Participant Information Sheet. If interested in participating, they will select a checkbox that takes them to the Consent Form and data protection policy to review on the trial electronic platform. Study eligibility and inclusion criteria will be clearly stated, and participants asked to electronically sign the Consent Form and date. The Consent Form asks for consent to undertake the initial and secondary screening, taking part in the trial as well as confirmation that the participant understands the nature of the study and meets inclusion criteria. Participants are asked to confirm that they meet each criterion. If eligible, participants will be asked to provide an e-mail address and mobile phone number.

If a participant completes the Consent Form and is eligible for the trial, they will be given an e-mailed confirmation that they are in the study, a unique study participant trial number and instructions indicating how, as per randomisation scheme, to download IonaFFV or Iona SHAM CONTROL on either an Android or Mac (IOS) based mobile phone. They are also provided with contact details (email, and/or telephone number as available) for the Lead Researcher if further study information is wanted or they are struggling to download IonaFFV or Iona SHAM CONTROL.

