### 8.4 Randomisation scheme

The feasibility RCT will follow MRC Complex Interventions Guidelines and relevant CONSORT reporting requirements with a pre-registered trial protocol. Randomisation will be in blocks of 3 with randomisation to the 2 arms (IonaFFV vs Iona SHAM CONTROL) conducted automatically by Qualtrics survey platform to minimise selection bias and maintain methodological rigor. Following randomisation IonaFFV or Iona SHAM CONTROL will be automatically sent a link to download the app.

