### 8.6 Method of implementing the randomisation/allocation sequence

Participants will be randomised by pseudorandom number generation. Eligible participants will receive an email confirmation which provides a download link and unique participant code to each participant accepted into the trial, and they will be prompted to download the app as soon as possible. Once selected according to the randomisation sequence either IonaFFV or Iona SHAM CONTROL, participants will download the app on their phone. Participants are blinded to the randomisation.

Should a participant fail to download the app and enter the code, an automated sequence of emails at the rate of 1 per day over a 7-day period will be sent to the participant reminding them to do so and reiterating the download and sign-up instructions. After this time no further contact with the participant will be made.

Detailed procedure for randomisation:

1. Participants are randomised in blocks of 3 (30 participants per arm) into the 2 arms (IonaFFV versus Iona SHAM CONTROL) on an intention-to-treat basis.
2. Block randomisation will continue until 60 (30 each arm) are randomised. As eligible participants complete the initial screening and demographics questionnaire they will be randomised in blocks of 3 to either the control or intervention arm by the Postdoctoral Research Associate or the Graduate Research Assistant.

3.       The system will record the allocation and the date randomised.

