### 9.2 SHAM control app

Participants randomised into Iona SHAM CONTROL app consisting of approximately the same number of lessons as Iona FV, with repeatable “meditation-like” exercises. The “meditation-like” lessons will consist of text, video and audio, similar to that of the IonaFFV app, and the exercises will again be text, video and audio, with the length of each lesson and exercise adapted to be approximately the same as the average engagement time per session with IonaFFV in order to match time on task for the user. Iona SHAM CONTROL will be delivered within the same app framework using approximately the same app and cloud infrastructure as IonaFFV to ensure a consistent look and feel and user experience across both apps. Similar to IonaFFV, notifications and emails will encourage the user to engage daily with the techniques with the aim of achieving a similar usage pattern between both apps. Iona SHAM CONTROL also contains modules on therapies that while commonly recognized are not evidence-based, such as Dream Analysis, again delivered using text, images and audio in a similar manner to IonaFFV. Such modules will be accompanied with related tooling such as a dream diary, presented similarly to the activity diary in IonaFFV, again with the aim of matching time on task and approximate user-experience to IonaFFV without containing any active evidence-based treatment.

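### Download codes come in two labelled sets, so one revealing email can decode all 60 allocations for staff who see the letters, and the unblinding rule covers analysis only

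*Protocol*

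**What the plan says.** Section 8.7 of the protocol has the app company supply codes in two groups: it "will provide a set of download codes for group A and group B". It continues that "The researchers will not know which group of codes contains the access to the intervention or control arm", and that "The researchers will randomly allocate these codes to eligible participants in blocks of 3". Section 8.6 likewise has randomisation done "by the Postdoctoral Research Associate or the Graduate Research Assistant", and 8.5 has university researchers do it with codes from the app company. Section 8.4 says something different: randomisation is "conducted automatically by Qualtrics survey platform to minimise selection bias". Section 6.3.1 gives the allocation details to one study researcher alone, so that the rest of the team stays blinded.

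Section 8.7 foresees that a participant's email may give away her arm. Its response is that "the researcher will notify the research team and will not conduct any analysis to allow the blinded researchers to conduct the analysis". Section 8.3 gives participants contact details "for the Lead Researcher if further study information is wanted or they are struggling to download IonaFFV or Iona SHAM CONTROL". Sections 8.7, 11 and 11.9 make the Lead Researcher the analyst. Section 8.5 relies on the Results being drafted under the letters A and B before the code is broken. Section 9.2 describes content found only in the sham app, such as Dream Analysis: "Such modules will be accompanied with related tooling such as a dream diary".

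**The concern.** If staff hand out codes from a set marked A or a set marked B, they know each woman's letter. The only thing hidden from them is which letter means IonaFFV, and that fact is the same for everyone. A message that mentions, for example, the dream diary discloses it.

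The rule in 8.7 addresses one consequence, the recipient's part in the analysis. It does not stop that person from allocating the remaining codes, dealing with participants, or checking adverse events and reactions, which 12.5 assigns to university researchers. It does not relabel the codes still to be issued. It requires a notice to the team but does not limit what the notice may say, so the notice could unblind others. The letters used to protect the drafting of the Results in 8.5 and the interpretation in 11.9 are the same letters that the message decodes.

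**Working it through.** The protocol gives no figure to reproduce here: 11.1 states that there is no sample size calculation, and no rate of revealing messages is given. The check is mainly a reading of who can see what.

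**Step 1. How much one disclosure reveals.** There are two letters and two arms, so two keys are possible (A active or B active). One letter paired with its arm leaves one key. The planned total is 60 (8.6). If the message arrives after 10 women are randomised, the key covers those 10 and the 50 to come: 10 + 50 = 60 of 60. With participant-specific codes, no shared label and the key held away from the recipient, the same message reveals 1 of 60.

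**Step 2. Who can pair sender and letter.**

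| Reader of the message | Sees the sender's letter? | Learns |
|---|---|---|
| Staff allocating codes (8.6, 8.7) | Yes | All 60 |
| Holder of the allocation details (6.3.1) | Yes | All 60 |
| Other team members (aggregated data only, 6.2 and 6.2.1) | No | One woman's arm, until A/B-labelled results are seen |

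Section 6.3.1 says that only the Lead Researcher can link ID numbers to people, and then that only one study researcher has the personal-data database and the allocation details. The natural reading is that these are the same person, though the protocol does not say so. The Lead Researcher is also the participants' contact (8.3) and the analyst (8.7, 11, 11.9). The likeliest recipient of a revealing message is therefore the person best placed to decode it, and the person whom the 8.7 rule would remove. The protocol names no replacement beyond the blinded researchers.

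**Step 3. Whether later allocations are exposed in advance.** Under 8.6 and 8.7 staff pick the code, so once the key is known the arm about to be given is known. Under 8.4 Qualtrics allocates, so the next letter need not be visible beforehand; each letter is decoded only once someone sees it recorded. The sections conflict, so this part of the problem is conditional.

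**Step 4. How likely is at least one revealing message?** Assume that each of 60 women independently sends one with probability q. The chance of at least one is 1 − (1 − q)^60:

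- q = 1%: 1 − 0.99^60 = 0.453
- q = 2%: 1 − 0.98^60 = 0.702
- q = 5%: 1 − 0.95^60 = 0.954

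The values of q are assumptions. The result is the chance of one or more messages. It becomes a chance of decoding all 60 only if the message reaches someone who can make the pairing in Step 2.

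**The case against.** A reader might infer that any single revealing email unmasks the whole trial. The documents do not support that. A recipient who lacks the letter list learns one arm, and 6.2, 6.2.1 and 6.3.1 are written to keep that list with one person. Nor do participants learn their own arm by this route. A reader might also infer that all later allocations become known in advance; under 8.4 they need not. And the 45%, 70% and 95% figures are not chances of whole-trial unmasking.

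The consequences are also limited. Women refer themselves, screening is online with fixed cut-offs (7, 8.2) and registration is automatic (6.1), so staff have little room to steer entry. Outcomes are self-completed on Qualtrics, and the apps have no human support (Table 10). Harm signals are largely PHQ-9 thresholds logged electronically, and doubtful relatedness goes to the steering and monitoring committees (12.4). Section 8.3 offers contact for study information or download trouble, and a woman who cannot download the app has not seen its content. Finally, 8.7 bars the recipient from all analysis, which suits a trial-wide disclosure.

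Most of this stands, and it narrows the point. It does not remove it. The single list holder in 6.3.1 appears also to be the contact and the analyst, and 8.6 and 8.7 put the letters in the hands of allocating staff as well. Section 8.7 itself expects revealing emails. The bar on analysis leaves allocation, event checking and the content of the notice uncovered.

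**Conclusion.** The point holds in a limited form. With two labelled sets, one revealing message decodes 60 of 60 allocations for anyone who can link sender to letter, and 1 of 60 for anyone else until labelled results appear. This contrast rests on the text of 8.7 and needs no assumed rate. How often such a message would arrive is unknown.

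The main harm is to allocation concealment (only if staff allocate), to event attribution, to the A/B-blinded drafting of the Results, and to the feasibility outcome in Appendix 1 that records whether blinding was maintained. The counterpart in 10.7 is worded for participant blinding, which this route does not break. Bias in selection and in self-reported scores is likely to be small. Because the trial's purpose is to settle methods for a definitive trial, a fragile code scheme is worth correcting now: the change should be made, but the feasibility counts do not depend on it.

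**What to change.** 1. Reconcile 6.3.1, 8.4, 8.5, 8.6 and 8.7 on who allocates and who sees the letter.
2. Use single-use, participant-specific codes with no group label visible to staff, released automatically by Qualtrics as 8.4 already states. Generate the sequence at the university, not at the app company, so that control of the order does not pass to the developer. Keep the code-to-arm key from the contact person and the analyst.
3. Attach the letters A and B only to the locked dataset.
4. Amend 8.7 so that a researcher who learns an allocation logs only the participant ID and date, does not pass on the content or the arm, and takes no further part in allocation, event assessment or analysis. This concerns arm information only, not the response to any safety concern in the message. State who analyses if the Lead Researcher is the one removed.

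The cost is a reformatted code list, reworded paragraphs and slightly more set-up, including someone at the university outside the contact and analysis roles to hold the key. The group letter would no longer be visible for ad hoc checks during the trial.

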### 8.8 Baseline data

Baseline data will be collected after participants sign the consent form but before randomisation. Here, data from second screening, if participants meet the study inclusion criteria, serves as baseline data. This is when the participant completes the PHQ9 and GAD7 on University of Exeter Qualtrics for the first time.

### 8.9 Trial assessments

Assessment will take place at baseline and then at 6 weeks post treatment start (equating to end of treatment) and 10-weeks post baseline representing the study endpoint. At both of these timepoints the participant will receive a request to complete the outcome measures with a URL included to take them to the UNIEXE Qualtrics page. The results of the assessments are only to collect research data for the trial and will not be provided to anyone outside of the study. The only exception to that would be if a participant indicates suicide risk and asks us to provide their assessment results to their medical practitioner. They would need to give written consent for this and provide us with the contact details to do so.

At the end of treatment, all participants will be asked to complete the MAUQ

to determine the acceptability and usability of the app.

**Table 9 Assessment Schedule**

| **Procedures** | **Initial screening** | **Baseline (second screening)** | **6 weeks post initial app engagement** | **4 weeks follow-up**  **(10 weeks post initial app engagement)** |
| --- | --- | --- | --- | --- |
| Informed consent | Yes | Yes | No | Yes |
| Demographics | Yes | Yes | No | No |
| Mental Health History | Yes | No | No | No |
| Eligibility assessment | Yes | Yes | No | No |
| Randomisation | No | Yes | No | No |
| Access to intervention | No | No | Yes | No |
| Assessment of wellbeing and depression | No | Yes | Yes | Yes |
| Assessment of current functioning | No | Yes | Yes | Yes |
| Assessment of usability and engagement | No | No | No | Yes |
| Feasibility outcomes | No | No | No | Yes |
| Adverse event assessments | No | No | Yes | Yes |

### 8.10 Long term follow-up assessments

Participants will be followed up at 6 (Treatment end) and 10 weeks post baseline (4 weeks follow up) post treatment end.

### 8.11 Payment

Participants will be paid £30.00 in electronic vouchers for completing the measures after completion of the 4 weeks follow up (10 weeks). Participants indicating, they wish to withdraw from the study will receive this payment.

- £20 for those who complete the 6-week questionnaire (but not follow up),

- £10 for those who drop out following downloading the app.

### 8.12 Withdrawal criteria

At any time, participants can choose whether they want to stop using the IonaFFV or Iona SHAM CONTROL intervention, or if they want to withdraw from the trial completely (including all assessments). A log will be kept of the participant number and date of all withdrawals from the trial. Participants who met the inclusion criteria at baseline will not be replaced. Participants that did not meet the criteria at baseline can be replaced and their data removed from the data set. Participants who withdraw from the trial will not be followed up. Once a participant withdraws from the study, they will still be able to use the app until the end of the study period if they choose.

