### 10.2 Outcome measures

**Table 11 Outcome measures**

| **Measure** | **Description** | **Reliability and Validity** |
| --- | --- | --- |
| **Primary/Feasibility/Methodological Outcomes** | | |
| **Feasibility** | To collect data on number of participants consented, recruited, completed screening, and to assess recruitment method, measure completion (baseline, 6 weeks, 10 weeks), drop out, drop out reason | NA |
| **Secondary Outcomes** | | |
| **Patient Health Questionnaire-9** (**PHQ-9**; Kroenke et al., 2001) | 9-item participant rated questionnaire assessing frequency of symptoms of depression over the last 2 weeks. 4-point scale for each item, with anchors at 0=not at all, 1 = several days, 2= more than half the days, 3 = nearly every day. Unidimensional scale. Available in English, Spanish, German, and Dutch versions. | Leading measure of depression widely used in clinical trials, clinical practice, and as part of the NHS Quality and Outcomes Framework (QOF) for UK primary care and Improving Access to Psychological Treatments (IAPT) Minimum Data Set (MDS). Cronbach’s α =0.89 in primary care, test-retest reliability (ICC) 0.84 after 48 hours. Validation studies indicate positive correlations with measures of functional status (r=0.73), disability days (r=0.39), and symptom-related difficulty (r=0.55) At cut-off of ≥ 10, excellent specificity (0.88) and sensitivity (0.88) with diagnoses of major depression by structured interview, replicated in a UK population (sensitivity 0.80; specificity 0.92). |
| **Generalised Anxiety Disorder-7 (GAD-7**; Spitzer et al., 2006) | 7-item participant rated questionnaire assesses frequency of symptoms of anxiety over the last 2 weeks. 4-point scale for each item, with anchors at 0=not at all, 1 = several days, 2= more than half the days, 3 =nearly every day. Unidimensional scale. Available in English, Spanish, German, and Dutch versions. | Leading measure of anxiety widely used in clinical trials, clinical practice, and as part of the UK NHS IAPT MDS. Cronbach’s α =0.92, test-retest reliability ICC = 0.83. Convergent validity good, r =.72 with Beck Anxiety Inventory, r = 0.74 with Symptom Checklist-90 anxiety scale. |

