### 11.4 Summary of baseline data and flow of patients

The analysis and presentation of the trial will be in accordance with CONSORT guidelines (Schulz et al., 2010). Recruitment, intervention uptake, outcome completion rates and attrition will be reported (with 95% CIs) and shown on a study flow diagram.

Participants may elect to withdraw from the study if they wish to do so at any time and for any reason (including perceived harms or lack of efficacy of intervention). This can be easily done by discontinuing use of the randomised app.

Participants will be withdrawn from the study entirely if discovered as ineligible at the time of recruitment. As a self-help psychological intervention, we do not anticipate significant iatrogenic effects or side-effects requiring individual discontinuation.

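### Drop-out reason is a listed primary/feasibility outcome, but no procedure is described to collect it when a participant leaves of her own accord, and sections 8.12 and 11.4 disagree on what counts as leaving

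*Protocol*

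**What the plan says.** The outcome is named twice. The study summary (Table 7) and Table 11 in section 10.2 both list, under primary/feasibility/methodological outcomes, "measure completion (baseline, 6 weeks, 10 weeks), drop out, drop out reason". Drop-out and its reason are separate items, so a count of losses does not supply the second.

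The procedures that bear on it are these:

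- Section 8.12, on the log: "A log will be kept of the participant number and date of all withdrawals from the trial".
- Section 8.12, on contact afterwards: "Participants who withdraw from the trial will not be followed up".
- Section 11.4 allows withdrawal "at any time and for any reason (including perceived harms or lack of efficacy of intervention"), and on how to do it says: "This can be easily done by discontinuing use of the randomised app".
- Section 8.6, on women who have not downloaded the app after seven daily emails: "After this time no further contact with the participant will be made".
- Section 8.11: "Participants indicating, they wish to withdraw from the study will receive this payment". It does not mention asking why.
- Section 12.4 places active withdrawals from treatment under monitoring, without mention of a reason.
- Table 10 in section 10.7 has a reason entry, but only for people screened out. Appendix 1 counts downloads, treatment completion and measure completion by arm. Neither table has a row for drop-out reason.

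Section 8.12 also opens by distinguishing a participant who stops using the app from one who leaves the trial altogether, assessments included. Section 11.4 makes no such distinction.

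**The concern.** The trial's principal objective (section 3) is to understand the methodological uncertainties of a definitive RCT, and the acceptability of and engagement with the app. Why women leave is central to that. Leaving because of questionnaire burden, a technical fault, an unhelpful app, worsening mood or improvement would each call for a different change to the next trial.

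The protocol itself treats leaving as informative. Section 11.4 expects that some will leave over perceived harm or lack of efficacy, and section 12.1 says disengagement is the likeliest course for users who do not benefit. Section 11.3 rules out imputation and relies instead on exploring patterns of missingness to inform the future design. Without reasons that exploration is much weaker, and the sham and active arms cannot be compared on why women left.

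This is a matter of data collection. A statistical analysis plan, however detailed, cannot analyse answers to a question that was never asked.

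**Working it through.** The protocol gives no figure to reproduce: section 11.1 states that there is no sample size calculation, and no attrition rate appears anywhere. The check is therefore to take each way a randomised woman can be lost and ask whether any described step obtains her reason.

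| Route | What the protocol provides | Reason obtained? |
| --- | --- | --- |
| Removed after a PHQ-9 item 9 elevation (11.8, 13.4) | Recorded as an adverse event; removed by the trial | Yes, by construction |
| Found to have been ineligible (11.4) | Removed by the trial | Yes, by construction |
| Tells the team she is withdrawing (8.11, 8.12) | Number and date logged; payment sent; no follow-up | Only if she volunteers it |
| Stops using the app without a message (8.12, 11.4) | Under 8.12 she can remain in assessments; under 11.4 she has withdrawn | Not asked under either reading |
| Never downloads the app (8.6) | Seven daily emails, then no contact | Not asked |
| Does not return the 6- or 10-week measures (8.5, 8.7) | Email and text reminders | Not asked |

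The first two routes yield a reason because the trial makes the decision. None of the four participant-initiated routes includes a question, form or field for it.

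The fourth row also exposes the conflict:

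- Under section 8.12, a woman who merely stops using the app has not withdrawn from the trial. She remains due for assessment and would receive the prompts planned in section 8.5.
- Under section 11.4, stopping the app is itself a way of withdrawing from the study. The rule in 8.12 against following up withdrawn women would then apply to her.

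The same woman is a retained participant in one section and a drop-out in the other. The drop-out count, the denominator for reasons and the set of women who receive 6- and 10-week requests all depend on which section is followed.

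For scale only, assume that 20% to 50% of the 60 randomised women are lost. This range is not from the protocol.

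- 0.20 × 60 = 12 women
- 0.50 × 60 = 30 women

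These are all losses. The number with no known reason would be smaller, by however many were removed by the trial or volunteered a reason.

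**The case against.** The best defence is that section 8.12 is incomplete rather than contradictory. It names two log fields without saying that they are the only ones. Table 11 states the intention "to assess recruitment method, measure completion (baseline, 6 weeks, 10 weeks), drop out, drop out reason", and Tables 9 and 12 schedule feasibility outcomes at 10 weeks. A reason column could sit in the electronic case report form or the data management plan, which are not shown. This stands in part: a reader might infer that the log excludes reasons, and the text does not say so. But an intention in an outcome table is not a procedure, and a 10-week assessment does not reach women who have already left.

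A reader might also infer that the outcome will have no data at all. The documents do not support that. Reasons are known for removals by the trial; some women announce their withdrawal (8.11); and all who are enrolled receive the Lead Researcher's contact details (8.3), so a reason can be volunteered.

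Nor do the documents support saying that every woman who stops the app slips out of contact. That follows from section 11.4 alone; under section 8.12 she can stay in follow-up.

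Finally, other data partly separate the kinds of loss: downloads and treatment completion by arm (Appendix 1), app log data (described in section 9.1 for IonaFFV), and the logging of elevated PHQ-9 scores in either app (13.1.2). These help to tell non-starters, disengagement and recorded deterioration apart. They do not show why a woman left.

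**Conclusion.** The point holds in this form: a named primary/feasibility outcome has no described means of collection for participant-initiated drop-out. If the protocol is followed as written, reasons will exist for trial-initiated removals and for women who volunteer them, and will otherwise be largely missing. Separately, sections 8.12 and 11.4 conflict on whether stopping the app is withdrawal from the trial, which leaves the drop-out group itself undefined.

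The number affected cannot be derived from the protocol; 12 to 30 women is only what the assumed 20% to 50% loss would give. The conclusion does not depend on that range. It rests on the protocol's text and would be softened if an unseen operational document already holds a reason field and an exit question. The change should be made before recruitment ends, because the information cannot be reconstructed after women have left.

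**What to change.** 1. In section 8.12, add a reason field to the withdrawal log, with an entry for none given.
2. Add one optional reason item, including prefer not to say, to messages already planned: the exchange in which a woman indicates withdrawal or is sent her payment (8.11), the final download reminder (8.6), and the 6- and 10-week reminder emails or texts (8.5, 8.7). Suitable options are burden, app not helpful, felt worse, felt better, technical problem and other. State that payment does not depend on answering. Section 8.11 describes no separate voucher-claim step, and no number of 6- or 10-week reminders is fixed, so the item should be attached to the messages themselves rather than to a claim form or a last reminder.
3. Add a row to Table 10 in section 10.7 and to Appendix 1: drop-out reason, by arm, with the share of drop-outs whose reason is known.
4. Reconcile sections 8.12 and 11.4, so that it is clear who counts as a drop-out and who stays in follow-up. Use the same definition in the flow diagram.

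The cost is one questionnaire item, one log column and a minor amendment. The downside is one optional question to women who are leaving. Response will be incomplete, which is why the share known should be reported. The right to leave without explanation is preserved.
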